### Interventions

2.7

Pharmacopuncture treatment will be performed by Korean neuropsychiatrists following the details of the Standards for Reporting Interventions in Clinical Trials for Acupuncture 2010 checklist (Table 1). Each participant will be scheduled to visit the institution twice a week for 8 weeks after screening and receive a total of 16 treatments of *H placenta* pharmacopuncture or placebo pharmacopuncture. 1 mL of *H placenta* or placebo will be injected twice a week into acupoints (GV20, both ST36, CV12). *H placenta* (Unimed Pharmaceutical, Seoul) is a pale-yellow transparent liquid contained in a brown ampoule. The content is 1 mL of *H placenta* extract per 1 mL. It should be stored in the shade in sealed containers at room temperature (1–30°C). Saline will be used as placebo; it is a colorless, clear liquid with a salty flavor. The content is 9 mg sodium chloride in 1 mL. Other drugs and therapies to ameliorate cognitive function are prohibited in principle during the clinical trial period, and in the event of concurrent treatment, the clinical trial director will determine whether the participant will be excluded from the study and the statistical analyses.

**Table 1 T1:** Details of acupuncture intervention (STRICTA).

Item	Detail	Description
Acupuncture rationale	(1a) Style of acupuncture	Pharmacopuncture
	(1b) Reasoning for treatment	The treatment was selected based on previous studies such as animal experiments and a case report.
	(1c) Extent to which treatment varies	None
Details of needling	(2a) Number of needle insertions per subject per session	4
	(2b) Names of points used (unilateral/bilateral)	GV20, CV12, ST36 (bilateral)
	(2c) Depth of insertion	5–10 mm
	(2d) Response sought	None
	(2e) Needle stimulation	None
	(2f) Needle retention time	None
	(2g) Needle type	0.30 mm × 8 mm, single use syringes (Becton, Dickinson and Company, USA)
Treatment regimen	(3a) Number of treatment sessions	16 sessions
	(3b) Frequency and duration of treatment sessions	2 sessions/wk for 8 wk
Other components of treatment	(4a) Details of other interventions administered to the acupuncture group	None
	(4b) Setting and context of treatment	Hospital outpatient department
Practitioner background	(5) Description of participating acupuncturists	Korean neuropsychiatrist or Korean medical doctor with an experience of more than 1-yr under the guidance of a Korean neuropsychiatrist
Control or comparator interventions	(6a) Rationale for the control or comparator in the context of the research question	Saline will be used as placebo control.
	(6b) Precise description of the control or comparator	Saline will be used as placebo control and will be inserted using the same syringe type into the same acupoints.

### Outcome measurement

2.8

#### Primary outcome

2.8.1

The primary outcome is the difference in mean change of MoCA-K scores between intervention group and control group. The MoCA-K is a tool that was originally developed by Nasreddin et al.^[21]^ to screen for MCI, which was translated into Korean and validated. It consists of 7 areas to evaluate memory, visuospatial/ executive function, naming, attention, language, abstraction, and orientation. The maximum score is 30 points, and 1 point is added when the participant has been educated for less than 6 years to correct differences in cognition due to academic background. It suggests a cutoff point of 22 or less for screening MCI,^[22]^ which means a decrease in cognitive function. Reliability of the original tool was Cronbach's α =.83^[21]^ and that of the translated tool was Cronbach's α =.81–.84.^[22]^

#### Secondary outcomes

2.8.2

Secondary outcomes are

(1)differences in mean change of MMSE-DS, K-DRS, CDR, GDS, K-BDI-II, STAI, STAXI, ISI, EQ-5D, EQ-VAS, and GQOL-D scores between intervention group and control group, and(2)direction of intra-group change of mean of K-DRS, MMSE-DS, MoCA-K, CDR, GDS, K-BDI-II, STAI, STAXI, ISI, EQ-5D, EQ-VAS, and GQOL-D scores in pre- and post-treatment evaluation. K-DRS, MMSE-DS, MoCA-K, GDS, K-BDI-II, STAI, STAXI, ISI, EQ-5D, EQ-VAS, and GQOL-D scores will be assessed at baseline and 8 weeks, and CDR score will be assessed at baseline, 4 weeks, and 8 weeks.

##### K-DRS

2.8.2.1

The K-DRS^[23]^ is the Korean version of the Dementia Rating Scale,^[24]^ which consists of 5 subtests suitable for examining general cognitive functions: attention, execution, organization, memory, and conceptualization. The score ranges from 0 to 144 points. The correlation with MMSE-K was 0.82, and 2-week test-retest reliability was 0.96.^[23]^ There was a significant performance difference between normal and dementia patients,^[23]^ and neurological validity was supported by structural brain magnetic resonance imaging (MRI) studies.^[25]^

##### MMSE-DS

2.8.2.2

The MMSE-DS was developed by Han et al (2010) to measure cognitive function in the elderly. It consists of 19 questions about time and place orientation, immediate and delayed recall, concentration, naming, repetition, visuospatial construction, reading and writing, abstract thinking, and judgement. The scores obtained are calculated by adding all the scores obtained based on the 19 questions. The maximum score is 30 points, and the cutoff score varies according to age, gender, and education. The Pearson correlation coefficient between 4-week interval test-retest results was 0.935 (*P* < .001).

##### GDS

2.8.2.3

GDS is designed to classify the clinical severity of patients who are suspected to have dementia or are diagnosed with dementia. It is a revised version of the GDS designed by Reisberg et al^[27]^ It is advantageous because the practitioner is able to easily determine and judge the severity of dementia in a relatively short time by comparing the degree of cognitive impairment described in each grade with specific examples. Reisberg et al showed that the inter-tester reliability is 0.95.^[27]^

##### K-BDI-II

2.8.2.5

The 21-item BDI was developed by Beck et al^[30]^ to measure the severity of depression. Items of the K-BDI-II are scored on a 4-point Likert scale ranging from 0 to 3 points, with a range of 0 to 63 points in total. A higher score means more severe depression. Depression severity is classified into 4 levels: normal (0–13), mild depression (14–19), moderate depression (20–28), and severe depression (29–63).

##### STAI

2.8.2.6

It is a measure that can evaluate state anxiety and trait anxiety simultaneously and was developed by Spielberger et al.^[31]^ In order to measure anxiety experience, it evaluates of state anxiety (20 questions) and trait anxiety (20 questions), each on a 4-point scale. The score ranges from 20 to 80, and a higher score means higher anxiety.

##### STAXI

2.8.2.7

The STAXI is a scale developed by Spielberger^[32]^ and consists of 44 questions that evaluate state anger, trait anger, and anger expression. Each item is measured on a 4-point scale and 5 subscales: state anger, trait anger, anger suppression, anger expression, and anger control.

##### ISI

2.8.2.8

This is a subjective measure of insomnia developed by Morin (1993), and a self-reporting measure that assesses the type and severity of insomnia, sleep satisfaction, disturbance of daytime function, and sufferings from sleep disorders. There are 7 items, and each item is scored from 0 to 5 points with the total ranging from 0 to 28. Higher scores indicate more severe symptoms of insomnia. The severity of insomnia is classified into 4 levels: normal (0–7), subthreshold insomnia (8–14), moderate insomnia (15–21), and severe insomnia (22–28).

##### EQ-5D, EQ-VAS

2.8.2.9

Euro Quality of Life (EuroQol) Group developed it as a tool for measuring health-related quality of life.^[34]^ It consists of a description part and evaluation part. The description part has 5 questions that measure the current health status 5 dimensions: mobility, self-care, usual activities, pain/discomfort, and anxiety/depression. Each dimension is rated by 3-level scale, which are no problem (level 1), moderate problem (level 2), and extreme problem (level 3). By combining the items answered from the 5 questions, there are potentially 243 different health states. Evaluation part consists of EQ-5D index and EQ-VAS. EQ-VAS using a visual analogue scale is designed to indicate one's current health status on a vertical line graded from 0 (the worst imaginable health) to 100 (the best imaginable health).

##### GQOL-D

2.8.2.10

GQOL-D is a scale to measure the quality-of-life of dementia patients, especially Alzheimer disease. It is designed to comprehensively cover all different sub-areas from other quality-of-life tools for the elderly^[35]^ A clinician conducts the assessment by an interview. This scale consists of a total of 15 items, including 13 items that measure physical health, psychological health, social relations, and environment and 2 items that respectively measure overall health and overall life satisfaction. The clinician asks a question and the subject indicates their quality-of-life and satisfaction, on a scale from 1 to 4 (1 = not satisfied, 2 = normal, 3 = satisfied, 4 = very satisfied). The total score is calculated from the sum of responses to each question, and the total score ranges from 15 to 60 points. The total score is converted into a standard score (T score) according to gender and age. The higher T score means the higher subjective quality-of-life and satisfaction of the subject. Conversely, the T score below 35T indicates significantly lower quality-of-life compared to the group of same gender and age.

### Sample size calculation

2.9

Since there were no previous clinical trials on *H placenta* for this indication, the results of previous studies on herbal medicines using MoCA scores^[36]^ were cited. According to the previous study comparing MoCA scores after herbal medicine or placebo treatment of patients with MCI, calculation using a standard formula^[37]^ yielded a sample size of 10 for each group, with 80% statistical power at 5% level significance (α=0.05, 1-β=0.8). Assuming a dropout rate of 30% considering the 8-week-long administration and follow-up period, the final sample size will be 15 for each group, 30 in total.

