### Statistical analysis

2.10

Among the demographic data, continuous data will be presented as mean and standard deviation, and categorical data will be presented as frequency and percentage. Group comparison of continuous demographic data will use the *t*-test if normality is satisfied in and the Wilcoxon rank sum test if normality is not satisfied. Categorical data will be compared using the Chi-square test or Fisher exact test.

The independent sample *t*-test will be applied for comparison of the difference in the mean change in parameter before and after the clinical trial between intervention group and the control group, and the Wilcoxon rank sum test can be applied when nonparametric analysis is required. In order to compare the difference in the change in trend by each group visit, data will be analyzed using repeated measures analysis of variance. All the statistical tests will adopt 2-tailed testing considering an alpha value of 0.05 with 80% power. Intent to treat will be mainly performed, but per-protocol will also be performed as a supplement.

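### Section 2.10 attaches 80% power to every test, but section 2.9 derives it for MoCA only, where 10 per arm reach 80% for a difference of about 1.3 SD

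*Protocol article*

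**What the plan says.** Section 2.9 borrows from one earlier herbal-medicine trial: "According to the previous study comparing MoCA scores after herbal medicine or placebo treatment of patients with MCI", a standard formula "yielded a sample size of 10 for each group, with 80% statistical power at 5% level significance". After a 30% allowance for dropout, "the final sample size will be 15 for each group, 30 in total". MoCA is the only scale named in this calculation.

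Section 2.8.1 defines the endpoint: "The primary outcome is the difference in mean change of MoCA-K scores between intervention group and control group". Section 2.8.2 lists 11 secondary scales for the same between-group comparison of change: MMSE-DS, K-DRS, CDR, GDS, K-BDI-II, STAI, STAXI, ISI, EQ-5D, EQ-VAS and GQOL-D.

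Section 2.10 plans t-tests on change, Wilcoxon rank sum tests where needed and repeated-measures ANOVA for trends over visits, with intention to treat as the main analysis. It then states: "All the statistical tests will adopt 2-tailed testing considering an alpha value of 0.05 with 80% power".

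**The concern.** Significance level and sidedness can be set by decree for every test. Power cannot: it follows from the sample size, the true difference and the variance of each outcome. The statement in 2.10 therefore presents as a design choice something that was worked out for one scale at most.

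The risk lies in how the results will be read. If the protocol says every test had 80% power, a non-significant result on sleep, mood, quality of life or a secondary cognitive scale may be taken as reasonable evidence against a benefit. With 10 to 15 per arm, the trial would miss a moderate benefit more often than it would find one. The same caution applies to MoCA-K unless the true effect is very large.

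**Working it through.** **Inputs.** Two-sided alpha 0.05 (2.10); power 80%, 10 per group before dropout, 30% dropout, 15 per group final (2.9); independent-sample t-test on change (2.10). The article prints no mean difference or SD.

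**Step 1: the plan's own figures.** The dropout step reproduces: 10 / (1 − 0.30) = 14.3, rounded up to 15 per group, 30 in total. The 10 per group cannot be reproduced forwards without a difference and an SD, so it is solved backwards.

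**Step 2: standardized difference d implied by 10 per group.**
- Normal formula: n = 2(z₀.₉₇₅ + z₀.₈₀)² / d², with 2(1.960 + 0.842)² = 15.70. So d = √(15.70/10) = 1.25.
- Noncentral t, two-sided, 10 per arm: d = 1.32 for 80% power.
- Noncentral t, 15 per arm (everyone analysed): d = 1.06.
- Wilcoxon, 10 per arm, taking an asymptotic relative efficiency of 0.955 under normality (an assumption): d = 1.36.

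**Step 3: power of the t-test at smaller effects.**

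| True difference | 10 per arm | 15 per arm | Per arm needed for 80% |
|---|---|---|---|
| 0.5 SD | 18.5% | 26.2% | 64 |
| 0.8 SD | 39.5% | 56.2% | 26 |
| 1.0 SD | 56.2% | 75.3% | 17 |

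These are fixed by n, alpha and d, so they apply to any of the 12 scales analysed by a t-test on change. For 80% power throughout, every scale would need a true effect of about 1.3 SD (10 per arm) or 1.06 SD (15 per arm).

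**Step 4: precision.** The half-width of a 95% CI for a difference is t × √(2/n) in SD units. With 10 per arm it is 2.101 × √(2/10) = 0.94 SD; with 15 per arm, 2.048 × √(2/15) = 0.75 SD.

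**Step 5: does the scale of the borrowed inputs matter?** Suppose they were post-treatment scores with d = 1.32. With equal SDs before and after and a pre-post correlation ρ (not given; a range is assumed), the SD of change is SD × √(2(1 − ρ)). Power for change with 10 per arm is then 66% at ρ = 0.3, 80% at 0.5 and 95% at 0.7. A mismatch could move power either way.

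**The case against.** The best defence is that the sentence in 2.10 is loose drafting: it repeats the design parameters of 2.9 and nobody computed power scale by scale. Section 2.1 also describes the aim as exploring efficacy and safety, so the trial does not present itself as confirmatory. Both points limit the seriousness, but the sentence still covers all tests, and no detail held in a fuller document could make it true at this sample size.

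A reader might infer more than the article supports:

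- *The 10 per group is wrong.* Nothing shows this. It is consistent with a large assumed effect, and the dropout step is correct.
- *The mean difference and SD are missing from the plan.* A journal article can leave them to the full protocol, so their absence here is not a fault.
- *The calculation used post-treatment scores instead of change.* The phrase in 2.9 describes the earlier study and does not say which quantity entered the formula. Even if it was post-treatment scores, power for change would rise when ρ exceeds 0.5. The retest values the article gives for related scales are high (0.96 for K-DRS, 0.935 for MMSE-DS), though they are not MoCA-K values.
- *The primary test falls short of 80%.* If the formula was the normal approximation, n = 10 corresponds to d from 1.25 up to √(15.70/9) = 1.32, and the t-test has about 75.5% to 79.8% power at exactly 10 per arm. The formula is not visible, however, and at the same effects 15 per arm give about 91% to 94%.
- *Saline injected at the same acupoints shrinks the contrast.* The Discussion does expect needling to contribute, but both arms receive it, and the article gives no basis for a size.

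**Conclusion.** The claim of 80% power for all tests does not hold. Section 2.9 supports it for MoCA only, and with 10 per arm it requires a true difference of about 1.3 SD (about 1.06 SD with 15 per arm). For effects of 0.5 to 1.0 SD, power lies between 18.5% and 56% with 10 per arm and between 26% and 75% with 15.

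These figures assume a two-sided 0.05 t-test with roughly normal data and equal variances. They do not depend on the unprinted inputs. The randomization section (2.6) can be read as 30 per group, against 15 per group in 2.9 and a total of 30 in Table 2. That is a separate contradiction, but it would not rescue the claim: 30 per arm reach 80% only at 0.74 SD and have 47.8% power at 0.5 SD.

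This is a misstatement of what the design can do. It does not show an error in the sample size calculation.

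**What to change.** - **Section 2.10:** keep two-tailed testing at 0.05 and delete the clause that gives all tests 80% power.
- **Section 2.9:** state that 80% power applies to the primary MoCA-K comparison only, at a standardized difference of about 1.3 with 10 completers per arm (about 1.06 with 15). Confirm that the borrowed difference and SD refer to change in MoCA, the quantity being tested; if they do not, restate the power on that scale.
- **Secondary comparisons:** describe them as exploratory, reported as estimates with 95% CIs, with non-significance not taken as evidence of no effect. This fits the aim in 2.1.

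The sample size, visits and tests stay as they are. The change is wording only, and the price is a less favourable power statement.

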### Statistical analysis

2.10

Among the demographic data, continuous data will be presented as mean and standard deviation, and categorical data will be presented as frequency and percentage. Group comparison of continuous demographic data will use the *t*-test if normality is satisfied in and the Wilcoxon rank sum test if normality is not satisfied. Categorical data will be compared using the Chi-square test or Fisher exact test.

The independent sample *t*-test will be applied for comparison of the difference in the mean change in parameter before and after the clinical trial between intervention group and the control group, and the Wilcoxon rank sum test can be applied when nonparametric analysis is required. In order to compare the difference in the change in trend by each group visit, data will be analyzed using repeated measures analysis of variance. All the statistical tests will adopt 2-tailed testing considering an alpha value of 0.05 with 80% power. Intent to treat will be mainly performed, but per-protocol will also be performed as a supplement.

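### The unadjusted t-test on MoCA-K change is valid, but it fixes the baseline slope at 1 and leaves a rank-test option open; a prespecified ANCOVA would serve a trial this small better

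*Protocol article*

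**What the plan says.** Section 2.8.1 of the protocol article defines the endpoint: "The primary outcome is the difference in mean change of MoCA-K scores between intervention group and control group". Section 2.10 tests it with an independent-sample t-test, which "will be applied for comparison of the difference in the mean change in parameter before and after the clinical trial between intervention group" versus controls. No baseline or centre term is mentioned. The sentence continues that "the Wilcoxon rank sum test can be applied when nonparametric analysis is required", without saying what makes it required. For demographic variables, the preceding paragraph is more definite and uses "the Wilcoxon rank sum test if normality is not satisfied".

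Section 2.8.2 gives the timing. MoCA-K is in the list of scales that ends "EQ-VAS, and GQOL-D scores will be assessed at baseline and 8 weeks, and CDR score will be assessed at baseline, 4 weeks, and 8 weeks". The primary outcome therefore has one baseline and one post-treatment value, and the covariate is already collected. Section 2.10 adds that, for trends over visits, "data will be analyzed using repeated measures analysis of variance". On planned size, Section 2.9 says that the calculation "yielded a sample size of 10 for each group, with 80% statistical power at 5% level significance"; after 30% dropout it arrives at 15 per group.

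**The concern.** With one baseline and one follow-up value, a change score is the special case of baseline adjustment in which the slope is set to 1. If the true slope is lower, subtracting the whole baseline over-corrects. This has two consequences. The variance of the treatment comparison is larger than it needs to be. And, given the baseline difference that actually occurs, regression to the mean moves the estimate in favour of the arm that started lower. A trial planned on about 10 evaluable participants per group has little precision to spare and cannot count on randomisation to balance baseline closely.

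The second part is the rank-test option. MoCA-K is an integer score with a maximum of 30, and each arm will have only 10 to 15 values, so the question of normality will predictably arise. A Wilcoxon test also does not estimate the difference in mean change that Section 2.8.1 names. As written, the article does not fix which p-value is primary.

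**Working it through.** **Inputs.** From the article: 10 evaluable per group, 80% power, two-sided alpha 0.05; 30% dropout; 15 randomised per group. Section 2.9 gives no effect size or SD, and no section gives r for MoCA-K. Both are treated as assumptions below. Section 2.6 speaks of 30 participants in each group, against 15 in Section 2.9. The two must be reconciled; 15 is used here because Section 2.9 and Table 2 (sample size 30) agree on it.

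**The plan's own figure.** The dropout step reproduces: 10 / (1 − 0.30) = 14.3, rounded up to 15 per group, 30 in total. The base figure of 10 cannot be checked without an effect and SD. Inverting the t-test power calculation at 10 per group gives an implied standardised difference in change of about 1.32.

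**Efficiency.** Assume equal variance s² at both times.
- Variance of change: 2s²(1 − r).
- Residual variance under ANCOVA: s²(1 − r²).
- Ratio: (1 + r)/2. The reduction in standard error is 1 − √[(1 + r)/2].

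Simulated power at 10 per group, with the effect set at 1.325 SDs of change (about 80% power for the t-test) and the ANCOVA containing group and baseline:

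| r (assumed) | Variance ratio | SE reduction | t-test power | ANCOVA power |
|---|---|---|---|---|
| 0.3 | 0.65 | 19% | about 80% | 92% |
| 0.5 | 0.75 | 13% | about 80% | 88% |
| 0.7 | 0.85 | 8% | about 80% | 83–84% |
| 0.8 | 0.90 | 5% | about 80% | 81% |
| 0.9 | 0.95 | 2.5% | about 80% | 79–80% |
| 0.935 | 0.97 | 1.6% | about 80% | about 79% |

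From about r = 0.9 upward, the cost of estimating the slope with so few participants cancels or slightly outweighs the smaller residual variance.

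**Chance imbalance.** With 15 per group the standard error of the baseline difference is √(2/15) = 0.365 SD. Given an imbalance δ, the change-score difference shifts by (1 − r)δ. For δ equal to 1 SE:
- r = 0.5: 0.5 × 0.365 = 0.18 SD
- r = 0.7: 0.3 × 0.365 = 0.11 SD
- r = 0.8: 0.2 × 0.365 = 0.07 SD

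The SE of the change-score difference is √[2(1 − r)] × 0.365, so the shift is √[(1 − r)/2] of that SE: 0.50, 0.39 and 0.32 in turn. An imbalance of at least 1 SE in either direction has probability P(|Z| ≥ 1) = 0.32.

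**Open choice of test.** Null simulations used integer-valued changes, normal or skewed, with 10 or 15 per group. A single test rejected in 4.1% to 5.1% of trials. Counting significance by either test gave 5.1% to 6.0%, so at most about one point above the nominal 5%. The two tests disagreed on significance in 1.6% to 3.1% of null trials and in about 5% to 7% of trials with a real effect.

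**Repeated measures ANOVA.** With two time points, its group-by-time test is identical to the t-test on change, so for MoCA-K it adds no further p-value.

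**The case against.** The strongest reply is that nothing here is an error. Endpoint and test match, the t-test is unbiased over randomisations and holds its level, and the stated aim in Section 2.1 is exploratory. All of that stands. What remains is an avoidable weakness in a method the article does state, not a detail it omits.

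The size of the gain also depends on an r that nobody has given. The only retest figures in the article are high: 0.96 over two weeks for K-DRS and 0.935 over four weeks for MMSE-DS. At such values ANCOVA gains nothing. But they concern other scales and shorter intervals, and this trial enrols only people with CDR 0.5, a restricted range that tends to lower r. So a claim that ANCOVA will certainly gain power is unsupported, and so is a claim that it will gain none.

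A reader might infer several stronger points that the document does not bear out:
- *That the baseline score is thrown away.* A change score uses it, with a fixed slope.
- *That a material imbalance is likely.* An imbalance of 1 SE or more occurs in about a third of trials, and the resulting shift is conditional on it, not a bias of the procedure.
- *That centre must be in the model.* There are two centres, but Section 2.6 describes block randomisation without mentioning stratification by centre, and adding centre in simulation brought no power.
- *That the Wilcoxon option seriously compromises the primary result.* The inflation is small, and Section 2.6 has the analysis done after database lock with groups labelled only A or B. That limits directed choice, although it does not settle which p-value is primary. The option may also be meant to carry the normality condition used for demographic data; the outcome sentence does not say so.

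**Conclusion.** The point holds as a recommendation about efficiency and prespecification. The planned test is valid. Baseline adjustment would raise power from about 80% to about 88% at r = 0.5 and 83 to 84% at r = 0.7, with almost no gain at 0.8 and a loss of about one point at most from 0.9 upward. It would also remove a conditional shift of 0.18, 0.11 or 0.07 SD (r = 0.5, 0.7, 0.8) at a 1-SE baseline imbalance. These figures rest on an assumed r, equal variances at the two times, normally distributed scores, an effect back-solved from the planned 10 per group, and 15 randomised per group. If 30 per group were correct, √(2/30) = 0.258 SD and the shifts fall to 0.13, 0.08 and 0.05 SD. The unfixed choice between t-test and Wilcoxon is a minor matter, worth closing because it costs nothing to do so.

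**What to change.** In Section 2.10, state the primary analysis as ANCOVA of week-8 MoCA-K on treatment group and baseline MoCA-K, reporting the adjusted mean difference with its 95% confidence interval. Name the Wilcoxon rank-sum test on change as a sensitivity analysis, to be reported whatever a normality check shows. Centre may be added but is optional unless randomisation is stratified by centre; if it is, centre belongs in the model.

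The adjusted difference still answers the question in Section 2.8.1: with baseline in the model, analysing week-8 score or change gives the same treatment estimate. The cost is about one sentence and one residual degree of freedom, with no new data, visits or participants. The downside is that there is no power gain, and possibly a loss of about one point, if r turns out to be about 0.9 or more. The change should be made before unmasked data are available.
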